      11. BMI
      12. Other potential confounders:
          1. Parents overseas born
          2. Occupation of both parents
          3. Second parent level of education
          4. Parity

The list of covariates to be included in the propensity score model will be finalised after consideration of potential open backdoor causal paths and conditioning effects of collider nodes. The list above will be used as start. Distinction will be made between the standard epidemiological definition of a confounder and the causal pathway definition.

**Causal pathway and confounding** *(excerpt from Causal Inference , What if. M Hernan & J Robins p85:* [*https://www.hsph.harvard.edu/miguel-hernan/causal-*](https://www.hsph.harvard.edu/miguel-hernan/causal-) *inference-book/*)

“..the bias has the same structure: it is due to the presence of a cause (known covariate L or unknown covariare U) that is shared by the treatment A and the outcome Y, which results in an open backdoor path between A and Y. We refer to the bias caused by shared causes of treatment and outcome as confounding,…”

**These potential confounders (PS_covariates) will then be used in the construction of a propensity score model for exposure assignment (vide infra).**

1. Handling of missing data using Multiple Imputation

a. Consideration of missing data will be confined to all the covariates identified for the construction of a (propensity score) model of the exposure status. When imputing these missing covariate values the imputation model will include include: the outcome; all covariates identified for inclusion in the propensity score model with any transformations and interaction terms where appropriate; as well as additional auxillary covariates* from the BOS database/NAPLAN/AEDC databases. *These co-variates will be selected once the data are available for review.

b. Multiple imputation will be performed using either Multiple Imputation by Chained Equations (MICE) and/or Missing Covariate Indicator Method (MCIM) and the imputed datsets will then be used for propensity score construction. Subjects with missingness greater than 50% of PS_covariates will be excluded from analysis, this proportion will be assessed and if substantial, may result in changes to the PS_covariate list used for ongoing analysis.

c Diagnostics will then be performed to assess the quality of the imputed datasets.

d. For each of these imputed datasets Inverse Probability Weights (IPW, vide infra) will be calculated and used in weighted regression analyses. For each outcome metric, average point estimates and standard errors (95% CI) appropriately adjusted, given the imputation framework, will be obtained. The number of imputed datasets will be set at a minimum of 20 with the number increased to equal to the highest percentage of missingness in the raw PS_covariate list (ceiling of 50% by design). Details of imputation and assessment of adequacy will be formally presented.

1. Development of Inverse Probability Weights.

a) For each imputed dataset, logistic regression with robust standard errors will be performed for the binary exposure against all the PS_covariates. Inverse probability weights will be calculated for each individual given their exposure and these will be used to weight the adjusted regression model.

b) For each imputed dataset the distribution of IPW by exposure status will be examined to ensure: (i) that there is common support (overlap) of the distributions adequacy of adjustment; and (ii) that the weighting was effective in equalizing the covariate distributions in the ‘pseudopopulation’. This will be performed using standardized difference (StD) constructed from the imputed mean minus the raw data mean for all PS_covariate, with an StD of less than 10% being considered adequate. Forrest plots comparing unadjusted and adjusted covariate distributions will also be performed.

1. Regression modelling
   1. All causal regression modelling wil be performed within the multiple imputation frame-work using the IPW propensity score-based weights.
   2. The outcome metric is considered to be absolute risk difference between IVF exposure groups. This will be performed using either generalized linear modelling with Poisson link to directly generate Relative Risks or via logistic regression modelling.
   3. Software: analysis will be performed using Stata v16 (StataCorp. 2019. *Stata Statistical Software: Release 16*. College Station, TX: StataCorp LLC. Causal inference will be performed using teffects commands (Treatment-effects estimation for observational data - see TE -teffects) run within within Stata’s multiple imputation suite.

*The* ***primary analysis*** *will focus on the* ***total effect*** *of IVF conception adjusted for common cause confounders. Part 4 outlines the proposed mediation analysis where* ***direct*** *and* ***indirect*** *(mediated) pathways (eg via prematurity) may be further investigated.*

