**CAUSAL RESEARCH QUESTION**

***What are the causal effects of Invitro Ferilization (IVF) v Natural Conception (NC) and IVF with Intracytoplasmic Sperm Injection (ICSI) v conventional IVF on the school-age developmental and educational outcomes for children?***

P – All Mothers (and their babies) who gave birth in Victoria during the period 2005-2018

*Note: we intend to consider mothers, fathers and children part of the target population even if we know that they do not have outcomes data available (e.g. AEDC)*

I – Conception via (i) any IVF; (ii) IVF with ICSI.

C – Conception via (i) natural conception (excluding ovulation induction (OI) and intra-uterine insemination (IUI)); (ii) conventional IVF.

O – Developmental and educational outcomes – AEDC and NAPLAN (Grade 3) scores.

T – The nominal age at which children are measured for AEDC (foundation school year: 4-6 years of age) and NAPLAN (school year level 3: 7-9years of age) are typically measured.

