**DATA SOURCES**

1. Victorian Perinatal Data Collection
   1. Approximately 1,000,000 Victorian births between 2005-2018
   2. Routinely-collected data from the electronic Birthing Outcome System (BOS).
2. Major IVF providers in Victoria
   1. Cycle data from all pregnancies that resulted in a birth from each of the following IVF providers 2005-2018 (approximately **30,000 cycles):**
      1. Melbourne IVF
      2. Monash IVF
      3. City Fertility Centre
3. Australian Early Developmental Census
   1. Performed *every three years* across Australia. These data are collected by prep school teachers who conduct an observational assessment of every child in their first year of full-time primary school.
   2. Birth data to be linked with corresponding AEDC data from 2009 (unlikely to link with births in our study cohort), **2012, 2015, 2018.**
   3. **Five domains of assessment:**
      1. Physical health and wellbeing – looks at absence from school due to illness, independence with toileting, coordination, fine motor skills and physical ability to climb stairs, and other aspects.
      2. Social competence – assesses ability to get along with peers, respect for adults and others, curiosity about the world and eagerness to play and learn, willingness to help other children who are hurt or having difficulty with an activity and problem-solving day-to-day tasks.
      3. Emotional maturity – aims to identify impulsive or bullying behaviour, as well as the child’s ability to make decisions, be patient and attentive, share and wait their turn in games.
      4. Language and cognitive skills – assesses ability to use English effectively; listen and follow instructions in addition to more in-depth assessments of reading, writing and numeracy.
      5. Communication skills and general knowledge – looks at the child’s ability to tell a story, participate in imaginative play, communicate their own needs to their peers and to adults and assesses their knowledge about the world (eg. the seasons, types of fruit, different animals etc).
   4. From the teacher’s assessment, an individual score is calculated for each child. Outcome measures include *both* a **score** (out of 10) and a **centile** for each domain for every child. Centile scores are used to define:
      1. *developmentally “vulnerable” = <10^th^ centile (in any domain)*
      2. *developmentally “at risk” = 10-25^th^ centile (in any domain)*

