**2. Population characteristics to be described:**

a) Overall cohort

b) Non-IVF cohort (naturally-conceived children) only

c) ART cohort overall (IVF, ICSI, IUI, OI)

d) IVF cohort only

e) ICSI cohort only

| **VARIABLE** | **DESCRIPTOR** |
| --- | --- |
| **Child baseline data** | |
| Sex | (% female) |
| Language Background Other Than English | (%) |
| Aboriginal / Torres Strait Islander | (%) |
| [*Mother born overseas*]  [*Father born overseas*]  Any parent born overseas | (%) |
| Birthweight | Mean and SD |
| Gestational age of delivery | Median and IQR |
| Plurality:  No. Twins  No. Triplets  No. Quads | Absolute numbers and % |
| Method of delivery | (% C/S) |
| **Maternal baseline data** |  |
| Maternal age | Median and IQR |
| Marital status:  Married/de facto  Single  Divorced  Widowed | (% of each category) |
| Level of maternal education:  Year 10 or below  High school  Trade/TAFE/diploma/certificate  Undergraduate Uni degree or above | (% of each category) |
| Maternal Occupation:  Senior management,  Other business manager, Tradesman/woman, clerks, sales and service staff,  Machine operators,  Not in paid work,  Not Stated/Unknown | (% of each category) |
| SEIFA (Socio-Economic Index for Areas) quintile:  1 (most disadvantaged)  2  3  4  5 (least disadvantaged) | (%) for each category |
| **Second parent baseline data** |  |
| Level of second parent education:  Level of maternal education  Year 10 or below  High school  Trade/TAFE/diploma/certificate  Undergraduate Uni degree or above | (% of each category) |
| Second Parent Occupation:  Senior management,  Other business manager, -Tradesman/woman, clerks, sales and service staff,  Machine operators,  Not in paid work,  Not Stated/Unknown | (% of each category) |
| **Childhood outcome data** |  |
| **AEDC** | |
| Individual score | Median (IQR) |
| Developmental vulnerability (<10^th^ in ≥2 domains) | % |
| **NAPLAN** |  |
| Scaled score | Median (IQR) |
| Z-score | Mean (SD) |
| Band category | N (%) |
| Binary – minimum standard | % |
| Public or private school | % (if data available) |

Numbers and characteristics of children for which NAPLAN outcome data was *not* matched or available will also be described given that NAPLAN is not compulsory.

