**STATISTICAL ANALYSIS**

**PART ONE – AEDC**

**Causal research question:** What is the causal effect of conception via IVF compared to natural conception on AEDC-defined outcomes for children?

**Exposure**: IVF conception.

**Primary outcome:** A score of <10^th^ centile in “2 or more” domains (Binary yes/no).

**Secondary outcomes:** A score in the lowest decile in each domain: 1) physical health and wellbeing, 2) social competence, 3) emotional maturity, 4) language and cognitive skills, and 5) communication skills and general knowledge.

**Inclusion criteria:** Children born in the study time period.

**Exclusion criteria:** Multiple pregnancies, known congential anomaly.

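### The target population includes children with no outcome, but missing-data handling covers covariates only, so the planned analysis is a complete-outcome analysis that does not estimate the declared effect

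*SAP*

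**What the plan says.** - **Target population.** Under Causal Research Question, the population is "All Mothers (and their babies) who gave birth in Victoria during the period 2005-2018". The note beneath keeps mothers, fathers and "children part of the target population even if we know that they do not have outcomes data available (e.g. AEDC").
- **Effect.** The box of causal-inference steps in Part One describes the effect as a comparison of outcomes averaged over the entire target population. It also asks that identifying assumptions be stated and that sensitivity to departures from them be assessed.
- **Inclusion.** Part One includes "Children born in the study time period", with no restriction by birth year or by availability of an outcome. Part Two words its rule almost identically.
- **Outcome data.** Data Sources describes AEDC as a three-yearly census of children in their first year of full-time school. The usable waves are 2012, 2015 and 2018; of the earlier wave it says: "Birth data to be linked with corresponding AEDC data from 2009 (unlikely to link with births in our study cohort").
- **Missing data.** Part One, multiple imputation, item a: "Consideration of missing data will be confined to all the covariates identified for the construction of a (propensity score) model of the exposure status". The outcome enters only as a predictor: "When imputing these missing covariate values the imputation model will include include: the outcome". The inverse probability weights are for exposure only.
- **Missing outcomes.** The closing note to the table of population characteristics says that the numbers and characteristics of children whose NAPLAN outcome "was *not* matched or available will also be described given that NAPLAN is not compulsory". There is no matching commitment for AEDC.

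Part Two takes over the imputation and weighting steps unchanged, and Part Three adopts the same methodology.

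**The concern.** The SAP declares one population and specifies methods that can only reach another. A weighted regression needs an outcome for every child in it. With no outcome imputation, no weight for outcome availability and no stated missing-outcome assumption, it runs on children with a recorded outcome and is then read as an effect over all births.

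Two kinds of absence are left undistinguished:

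- **Calendar absence.** The child's foundation year was not an AEDC year, or the Grade 3 year lies outside the NAPLAN years held. This changes which birth cohorts, and which era of IVF and ICSI practice, the result describes.
- **Selective absence.** A child who could have been assessed was not, or moved away, or was not linked. If this depends on ability and on mode of conception beyond what the covariates capture, it can bias the IVF contrast itself.

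The SAP also does not say in which set of children the imputation, propensity and balance models are fitted. The outcome must enter the imputation model, yet most included births have no AEDC outcome.

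**Working it through.** The SAP gives no AEDC coverage figure, so there is none to reproduce. Coverage can be derived from its own inputs.

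**Inputs from the SAP**
- Birth years: 2005 to 2018, so 2018 − 2005 + 1 = 14.
- Births: about 1,000,000. IVF cycles resulting in a birth: about 30,000.
- Usable AEDC waves: 3, each covering one school intake.
- Age at AEDC: 4 to 6 years.

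**Assumptions added**
- Equal births, and equal IVF births, in each year.
- One intake equals one birth year's worth of children.
- Full linkage, varied below.
- No allowance for the exclusion of multiple pregnancies and anomalies.

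**AEDC coverage** = usable waves / birth years × linkage rate
- Full linkage: 3/14 = 21.4%. Births: 1,000,000 × 3/14 ≈ 214,000. IVF: 30,000 × 3/14 ≈ 6,400.
- Linkage of 90%, 80% and 70% (assumed): 19.3%, 17.1% and 15.0%.
- Ceiling if the 2009 wave also linked in full, which the SAP calls unlikely: 4/14 = 28.6%.

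**Which births can appear** (wave year minus age 4 to 6)
- 2012 wave: births 2006-2008. 2015 wave: births 2009-2011. 2018 wave: births 2012-2014. Each wave takes one intake from its range.
- A child born in 2015 or later is at most 3 years old in 2018. Births 2015-2018, 4/14 = 28.6% of birth years, cannot have an AEDC record.

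**NAPLAN.** The test is annual, but the SAP does not state which years are held. If the last year were 2018 to 2021 and Grade 3 age 8 or 9 (assumed), the reachable birth years run from 5/14 = 36% (2005-2009) to 9/14 = 64% (2005-2013). The one-fifth figure is for AEDC only.

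**How each kind of absence acts** (illustrations on assumed values, not estimates)
- *Calendar.* If the risk difference were 0 in covered births and 1.0 percentage point in the rest, the effect over the declared population would be (1 − 0.214) × 1.0 = 0.79 points, while the analysis would report 0. If the effect is the same in both, nothing is lost.
- *Selective.* Take a true risk of 10% in both groups. Let vulnerable IVF children be observed at a fraction r of the rate of other children, with no such selection after natural conception. The apparent IVF risk is 0.10r / (0.10r + 0.90). For r = 0.95, 0.90 and 0.80 the apparent difference is −0.45, −0.91 and −1.84 points. The SAP gives nothing from which r could be set.

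**The case against.** **The one-fifth figure is not a bias.** Whether a child's foundation year falls in a wave year is set by birth date and school entry. Given birth year, that is plausibly unrelated to the child's result. A reader might infer from four-fifths of births lacking AEDC that the IVF contrast is badly distorted. The SAP does not support that; nothing in it suggests that the effect differs between covered and uncovered birth years. This part of the objection stands, and the calendar absence should be treated as a question of population.

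**The weights may be fitted only in assessed children.** A reader might infer that weights are built on all births and so fail to balance the subset with outcomes. The SAP does not say so. Age when assessed heads its starting list of confounders and is undefined for an unassessed child, which points the other way. This also stands: the defect is that the set is unstated, not that imbalance has been shown.

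**Complete-outcome analysis can be valid.** If outcomes are missing at random given exposure and the modelled covariates, an adjusted complete-outcome analysis can be sound for the eligible children. SEIFA, maternal education, LBOTE and ATSI are among the adjustment variables and cover part of the family-background route. This is true, but the SAP does not state that assumption, and it would not extend the result to cohorts that no wave covers.

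**The SAP is open about the gap.** It names children without AEDC, lists the usable waves, promises a description of unmatched NAPLAN children and mentions sensitivity analysis in general terms. The flow chart is not shown and may display the analysed subsets. Silent deletion would therefore be an unfair charge. None of this supplies a method, however, and the missing-data section expressly limits its scope to covariates.

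**Conclusion.** The point holds as a mismatch between the declared effect and the planned analysis. The target is all births, including those with no outcome; the analysis can use only children with one; and no assumption joins the two. It affects Parts One and Two directly, and Part Three because it uses the same methods.

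For AEDC, about 21% of births can have the outcome under equal births per year and full linkage (15% at 70% linkage; at most 29% with a complete 2009 wave). For NAPLAN the share cannot be fixed without the test years held.

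The size of any bias cannot be computed from the SAP. Simple NAPLAN scenarios show why no figure should be claimed. The shift is the difference in missing share times the score gap between observed and missing children. A 4-point difference with a 0.4 SD gap gives 0.04 × 0.4 = 0.016 SD; a 10-point difference with a 0.5 SD gap gives 0.10 × 0.5 = 0.05 SD, half the SAP's mild threshold of 0.1 SD. Those inputs have no source in the document and ignore covariate adjustment. A reader might take them as evidence of bias; they show only that selective absence deserves a check.

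Severity: should be fixed. The remedy is cheap, but harm to the IVF contrast is possible rather than shown.

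**What to change.** 1. **Align population and data.** Restrict the target and analysis sets of Part One to birth cohorts whose foundation year is a held AEDC year, and those of Part Two to cohorts whose Grade 3 year is a held NAPLAN year. State the NAPLAN years. Because the age bands span several birth years, define eligibility by an explicit birth-date window. Fit the imputation, propensity and balance models in these sets, and say so.
2. **Cover missing outcomes.** Delete the wording that confines missing-data handling to covariates, and state the missing-outcome assumption. Among eligible children, either multiply the exposure weight by 1 / P(outcome observed | exposure, perinatal covariates) or impute the outcome. The availability model should use variables recorded at birth, since those recorded only at assessment are absent for unassessed children. Report the result beside the complete-outcome analysis.
3. **Describe both gaps.** Tabulate AEDC non-matches by exposure group, as well as the unmatched NAPLAN children already planned for description.

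The cost is revised SAP wording, one extra model per outcome source, slightly wider intervals and a narrower stated population. No listed source promises reasons for absence, so withdrawal, migration and failed linkage may have to be modelled together.

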**Causal Inference methodology**

The analysis steps 1, 2 and 3 will be identical for that detailed above for Part One (AEDC outcome) and are not repeated here.

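### The imputation model for missing confounders is listed without the exposure, so under chained equations the propensity weights under-correct and the estimates lean towards the crude contrast

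*SAP*

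**What the plan says.** All references are to the SAP.

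- **What is imputed** (Part One, Handling of missing data using Multiple Imputation, item a): "Consideration of missing data will be confined to all the covariates identified for the construction of a (propensity score) model of the exposure status".
- **What the imputation model contains** (same item): "the imputation model will include include: the outcome; all covariates identified for inclusion in the propensity score model with any transformations and interaction terms", and then "as well as additional auxillary covariates* from the BOS database/NAPLAN/AEDC databases". The auxiliaries are to be chosen once the data can be seen.
- **Method** (item b): the choice is left open between "Multiple Imputation by Chained Equations (MICE) and/or Missing Covariate Indicator Method (MCIM"). The resulting datasets "will then be used for propensity score construction".
- **Use of the imputed data** (Development of Inverse Probability Weights, item a): in each imputed dataset, "logistic regression with robust standard errors will be performed for the binary exposure against all the PS_covariates". The weights from this model adjust the outcome regression.
- **Reach**: for NAPLAN, "The analysis steps 1, 2 and 3 will be identical for that detailed above for Part One". Part Three states that the same methodology applies to ICSI.

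The exposure is therefore the dependent variable of the propensity model but is not on the list of imputation predictors. It is not a propensity covariate. Nor do the named auxiliary sources include the IVF providers' cycle data, which Data Sources lists as a separate source.

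**The concern.** An imputation model should contain every variable whose relation to the imputed covariate matters in the later analysis. Here the main such relation is between covariate and exposure, because the propensity score is built on it. If exposure is left out, each missing value is drawn as if the covariate were independent of exposure given the outcome and the other covariates. For a confounder that is not true.

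The imputed values then carry too small a difference between IVF and natural conception, or between ICSI and conventional IVF. The fitted propensity model understates the association and the weights remove only part of the confounding. What remains has the direction of the crude difference. Adding imputations does not reduce it, because it is bias and not Monte Carlo error. All primary contrasts share the step, so all would carry it.

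**Working it through.** The SAP states no figure on this point, so there is nothing to reproduce. The direction and size of the effect were checked by simulation.

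**Inputs from the SAP**
- Exposure prevalence: about 30,000 IVF cycles resulting in a birth and about 1,000,000 births (Data Sources), so 30,000 / 1,000,000 = 3%.
- Effect-size scale for NAPLAN: 0.1, 0.2 and 0.4 SD as mild, moderate and extreme (Part Two, Regression modelling).

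**Assumptions, because the SAP gives no values**
- True exposure effect 0.
- One standardised confounder X, missing completely at random in 10%, 30% or 50% of records, and one fully observed covariate Z, correlated 0.3 with X.
- X raises the log-odds of exposure by 0.5 per SD. Its slope on the outcome is 0.1, 0.2 or 0.3 SD per SD.
- A stronger case (log-odds 0.7, slope 0.4) and a 50% exposed share, standing in for ICSI v conventional IVF, were also run.

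**Method.** X was imputed by proper normal-linear draws from {Z, outcome}, as the SAP lists, or from {Z, outcome, exposure}. Each completed dataset then had a logistic propensity score, inverse probability weights and a weighted mean difference, averaged over imputations. Bias = (estimate after imputation) − (inverse-probability-weighted estimate from complete data).

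**Results, 3% exposed, exposure omitted (SD units; ranges are over repeated runs)**

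| Outcome slope | 10% missing | 30% missing | 50% missing |
|---|---|---|---|
| 0.1 | 0.004 | 0.011 | 0.025 |
| 0.2 | 0.009 | 0.023-0.028 | 0.043-0.047 |
| 0.3 | 0.010-0.015 | 0.038-0.041 | 0.057-0.067 |

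Worked cell, slope 0.3 and 30% missing, from one run: crude difference 0.225, complete-data estimate 0.005, estimate with exposure omitted 0.043. Bias = 0.043 − 0.005 = 0.038 SD. Share of confounding left = 0.038 / (0.225 − 0.005) = 17%.

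**Variations**
- Stronger confounding, 3% exposed: 0.022 − 0.001 = 0.021, 0.077 − 0.011 = 0.066 and 0.107 − 0.001 = 0.106 SD at 10%, 30% and 50% missing.
- 50% exposed, log-odds 0.5, slope 0.3: 0.013 − 0.001 = 0.012, 0.035 + 0.002 = 0.037 and 0.054 + 0.007 = 0.061 SD.
- Correlation of Z with X raised to 0.7, slope 0.2, 3% exposed: 0.005, 0.017 and 0.024 SD, roughly half to two thirds of the 0.3-correlation figures.
- Binary outcome for AEDC (assumed prevalence about 10%, confounder log-odds 0.4 per SD): about 0.2, 0.4 and 0.8 percentage points, against a crude bias of about 2 points.
- Exposure added to the imputation model: bias at most about 0.006 SD in absolute value in every setting, which is mostly simulation noise.

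**Would the planned checks show it?** A comparison of exposed with unexposed in the weighted imputed data would not, because the weights balance the values as imputed. The SAP's standardised difference is defined as imputed mean minus raw mean, with a 10% limit. Computed within the exposed group, that gap was 0.04, 0.13 and 0.22 SD at 10%, 30% and 50% missing. It would pass at 10% and fail at 30% and 50%. Pooled over exposure groups it would miss the problem.

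**The case against.** **Omission, not exclusion.** The SAP says what the model will include. It does not call the list complete or rule the exposure out, and a competent analyst might add it. That stands as a description of the text. But the list names the outcome and not the exposure, and a programmer following it would leave the exposure out.

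**The missing-indicator route.** Item b permits it, alone or alongside chained equations. It has no imputation model, so the mechanism does not arise there. This stands and limits the point to the chained-equations route.

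**Related covariates.** A reader might infer that imputed confounders would show almost no group difference. They would keep the part predicted by the outcome, the other covariates and the auxiliaries. The SAP lists several related socioeconomic variables, and better prediction shrinks the bias, as the 0.7-correlation run shows. The difference is attenuated, not erased.

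**The 50% figure.** A reader might take "highest percentage of missingness in the raw PS_covariate list (ceiling of 50% by design") as an expected missing rate. It is a ceiling used in setting the number of imputations, tied to a per-subject exclusion limit. The SAP gives no missing rate.

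**Detectability.** A reader might infer that no diagnostic could reveal the problem. That is too strong. The imputed-minus-raw comparison could, if made within exposure group and with substantial missingness. The SAP also promises imputation diagnostics and a report on adequacy.

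**Yardstick.** Expressed in standard errors the bias can look large, since the cohort is very large. The SAP itself expects statistical significance and judges by magnitude, so SD units are the fair measure. On that scale the bias stays below 0.1 SD under moderate confounding. It passes 0.1 SD only with the stronger assumed confounding at 50% missing.

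**Conclusion.** The point holds for the chained-equations route. As listed, the imputation model omits the variable that the propensity model regresses on the imputed covariates, and the consequence is under-adjustment in Parts One to Three.

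The size is conditional on assumptions the SAP does not settle: missing rate, confounder strength and how well other covariates predict the missing one. Under moderate confounding, NAPLAN bias is about 0.004-0.015 SD at 10% missing, 0.01-0.04 SD at 30% and 0.02-0.06 SD at 50%. Single runs vary a little around these limits. The simulation has one partly missing confounder and values missing completely at random, so it is a guide to scale and not a forecast.

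The documents do not support saying that the primary results would be seriously distorted. They support saying that a systematic bias towards the crude contrast is built in, usually smaller than the SAP's mild threshold, and not reliably caught by the checks as described.

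**What to change.** In Part One, Handling of missing data, item a, list the exposure as a required term in the imputation model, alongside the outcome, the propensity covariates and the auxiliaries. It must be present for each contrast. One way is a single variable with the levels natural conception, conventional IVF and ICSI, so that the same imputations can serve Parts One to Three. Interactions of exposure with other terms, or imputation within exposure group, are optional refinements and not needed to cure the defect.

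The cost is one phrase in the SAP and one more predictor in each chained equation, with no new data to collect.

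### The missing-data step counts the Missing Covariate Indicator Method as multiple imputation, permits it in place of MICE or with it, and fixes no primary method

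*SAP*

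**What the plan says.** The text is in SAP Part One (AEDC), Causal Inference methodology, under the step on missing data.

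- **Item a** limits the step to the propensity-score covariates: "Consideration of missing data will be confined to all the covariates identified for the construction of a (propensity score) model of the exposure status". It then sets the content of the imputation model: "When imputing these missing covariate values the imputation model will include include: the outcome; all covariates identified for inclusion in the propensity score model", plus auxiliary variables. The exposure is not named.
- **Item b** gives the method: "Multiple imputation will be performed using either Multiple Imputation by Chained Equations (MICE) and/or Missing Covariate Indicator Method (MCIM"). It adds that "the imputed datsets will then be used for propensity score construction", and that "Subjects with missingness greater than 50% of PS_covariates will be excluded from analysis".
- **Item c** requires diagnostics on the quality of the imputed datasets.
- **Item d** sets the number of datasets: "The number of imputed datasets will be set at a minimum of 20 with the number increased to equal to the highest percentage of missingness". It also says: "For each of these imputed datasets Inverse Probability Weights (IPW, vide infra) will be calculated and used in weighted regression analyses", with standard errors adjusted for the imputation.

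The Regression modelling step then places all causal modelling inside the multiple-imputation framework. Part Two (NAPLAN) takes over the same steps unchanged, and Part Three (ICSI) uses the same methodology.

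**The concern.** MCIM and MICE are different kinds of method. MICE draws plausible values from a model several times, and the spread between the completed datasets enters the standard error. MCIM sets the missing value to a constant and adds an indicator to the propensity model. It draws nothing and produces one dataset. The SAP nevertheless lists both as ways of doing multiple imputation, and does not say which is primary or which covariates each would serve.

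Two things are at stake. First, the choice between methods with different bias properties is left open until the data are in hand. Second, the primary analysis is meant to give the total effect after removing shared causes of exposure and outcome. Part Four names SEIFA, LBOTE, maternal education and ATSI as variables to be adjusted for by weighting in all analyses. If one of these is missing and only MCIM is used, the weights for those children cannot use it.

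The study draws on about 1,000,000 births, and Part Two itself expects differences to be highly significant. Systematic error therefore matters more here than sampling error.

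**Working it through.** **1. Does MCIM fit the surrounding items?** The SAP states no figure to reproduce, so the items are compared directly.

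| SAP requirement | MICE | MCIM alone |
|---|---|---|
| Item a: imputation model containing the outcome | yes | no imputation model exists |
| Item c: diagnostics of imputed datasets | yes | no imputed values to examine |
| Item d: at least 20 datasets | yes | one dataset |
| Item d: standard errors adjusted for imputation | yes | no between-imputation variance |

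An MCIM-only analysis therefore conflicts with three of the four items in its own step.

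**2. What bias would MCIM alone leave?** Take one binary confounder, a true effect of zero, and values missing completely at random in a share m.

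- Where the covariate is recorded (share 1 − m), the weights balance it and the weighted difference is 0.
- Where it is missing (share m), the propensity score is constant, so the weighted difference equals the crude one.
- Overall: residual bias = (1 − m) × 0 + m × crude = m × crude.

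**3. AEDC illustration (risk difference).** All inputs are assumptions: confounder prevalence 50%; exposure 3% without the confounder and 7% with it; outcome risk 14% without and 7% with.

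- Exposed risk: (0.5 × 0.03 × 0.14 + 0.5 × 0.07 × 0.07) / 0.05 = 0.00455 / 0.05 = 9.10%.
- Unexposed risk: (0.5 × 0.97 × 0.14 + 0.5 × 0.93 × 0.07) / 0.95 = 0.10045 / 0.95 = 10.57%.
- Crude difference: −1.47 percentage points, all of it confounding.

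**4. NAPLAN illustration (SD units).** Assumed confounding by the covariate: 0.10 SD. Part Two sets 0.1 SD as its smallest clinically meaningful effect.

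| Share missing | AEDC residual bias (points) | NAPLAN residual bias (SD) |
|---|---|---|
| 5% | −0.07 | 0.005 |
| 10% | −0.15 | 0.010 |
| 20% | −0.29 | 0.020 |
| 30% | −0.44 | 0.030 |
| 50% | −0.74 | 0.050 |

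The 50% row is not a guaranteed upper limit. The exclusion rule in item b works per child across covariates, so it does not cap missingness in any single covariate.

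**5. Simulation check.** There were 400,000 children and 8 replicates per scenario, with a binary outcome, a logistic propensity score and a second, fully observed covariate. That covariate was either unrelated or related to the one with missing values. Missingness was completely at random, or dependent on exposure and the second covariate.

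| Share missing (about) | MCIM minus full-data IPW (points) |
|---|---|
| 10% | −0.15 to −0.19 |
| 30% | −0.45 to −0.54 |
| 50% | −0.72 to −0.84 |

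Imputation with exposure and outcome in the model stayed within 0.04 points of the full-data estimate in every scenario. Having the second covariate related to the missing one reduced the MCIM bias only slightly or not at all.

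**The case against.** **MCIM alone may not be intended.** The connective in item b also covers MICE with missingness indicators added, which does impute. Items a, c and d and the Regression modelling step all presuppose true imputation. A reader might infer that an MCIM-only primary analysis is planned; the SAP does not say so. What stands is that item b permits it and nothing ranks the options.

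**Other covariates still work.** A reader might infer that all confounding is left uncontrolled in children with a missing value. It is not. Only confounding by the missing covariate itself remains, and the SAP lists more than a dozen other candidates that still enter the weights. They may absorb part of it, although the one related covariate simulated here absorbed little.

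**MCIM can be valid.** It is valid in a propensity score if the covariate does not confound when it is unrecorded. MICE in turn relies on values being missing at random. Both points are fair, but the SAP neither states nor defends the MCIM condition, although its own list of causal-inference steps asks for assumptions to be stated.

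**The sizes are assumed.** This stands in full. Every NAPLAN value in the illustration is below 0.1 SD, and at low missingness the bias is very small.

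**The comparator is not the plan's MICE.** The simulated imputation included the exposure, which item a does not name. Deleting MCIM would not by itself secure the simulated performance.

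A reader might also suppose that the planned standardized-difference check fails specifically under MCIM. As defined, it compares imputed with raw means rather than exposure groups, so it has the same weakness under MICE. That is a separate matter.

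**Conclusion.** The concern holds in a limited form. Two defects are firm because they rest on the text alone: MCIM is mislabelled as multiple imputation, and no primary method is fixed. The conflict with items a, c and d is equally clear if MCIM is used alone.

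The bias is conditional. It arises if MCIM is used alone and the covariate still confounds when unrecorded. It concerns that covariate only, and under missing completely at random it is about the missing share times that covariate's confounding. Over 5% to 50% missing, this is 0.005 to 0.05 SD for an assumed 0.10 SD of confounding, or 0.07 to 0.74 percentage points for an assumed crude difference of 1.47 points. The SAP gives neither missingness nor confounding strength, so the bias in this study cannot be stated. The plan should be corrected, but it does not follow that its results will be materially biased.

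**What to change.** - **Item b:** name MICE as the only primary method and remove MCIM from the sentence on multiple imputation.
- **Item a:** add the exposure to the outcome, propensity-score covariates and auxiliaries in the imputation model.
- **MCIM, if kept:** describe it separately as a sensitivity analysis, state the assumption that the covariate does not confound when unrecorded, do not call it multiple imputation, and place it outside the rule of 20 or more pooled datasets.

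The cost is a wording change in two items, plus computing time for MICE on a large linked file. The primary analysis would still rely on values being missing at random, which the SAP should state. A sensitivity analysis resting on a different assumption would then have a clear purpose.
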